### Treatment Conditions

Usual care includes a booklet with brief instructions on postoperative care and surveillance of complications provided during hospitalization, and a general assessment and some instructions regarding medication intake and safe return to activities as needed at the time of the follow-up appointment. In addition to usual follow-up care, in the first week of enrollment, the ACG will have access to a 15-minute standardized educational web-based session on persistent postsurgical pain, how pain and stress may interact, and their potential impact on recovery. Brief instructions on self-care (eg, selecting activities that bring a sense of pleasure or mastery) and helpful self-statements (eg, “I will overcome this pain” and “this pain will not last”) will also be provided. In addition, three weekly reminders will be sent to encourage participants to review the web-based session.

Patients assigned to the EG will receive a brief web-based MBCT intervention adapted from the brief four-session clinical manual on MBCT for chronic pain by day [84]. Four 15- to 30-minute sessions are planned (Textbox 1). Each session is structured as follows: an introductory video of the clinician, mindfulness exercise audio recording, wrap-up and weekly homework, or maintenance instructions from the clinician.

Outline of the four brief mindfulness-based cognitive therapy sessions.
**Sessions’ Main Themes and Mindfulness Strategies**
Session 1: persistent postoperative painBody scan (20 minutes)Session 2: stepping out of automatic thoughtsMindful breathing (10 minutes)3-minute breathing spaceSession 3: acceptance and self-care activitiesMindful breathing (10 minutes)Session 4: wrap-up and maintenance plan3-minute breathing spaceBody scan (20 minutes)

The first session will first focus on providing feedback regarding persistent postsurgical pain, the role played by the brain in pain perception, and the relationships between thoughts, feelings, and behaviors. It will end with teaching one mindfulness strategy, that is, body scan, or bringing detailed awareness to each body part and bodily sensation, which is considered an accessible introductory exercise to mindfulness meditation [47]. The second session will focus on pain-related automatic thoughts and teaching the second mindfulness strategy, that is, mindful breathing or focusing attention on breathing—the inhale and the exhale. Moreover, a brief portable 3-minute breathing space strategy will also be presented. The third session will focus on acceptance and self-care strategies and practicing mindful breathing. The fourth session consists of providing feedback and reminders about cognitive reactions to pain and suggesting a maintenance plan along with an opportunity to practice the strategies. The participants will be asked to practice guided meditation (audio recording) 5 days a week for a total of 4 weeks: beginning with body scan in week 1, mindful breathing and the 3-minute breathing space in week 2, and participants may choose either practice for weeks 3 and 4. Participants will also receive a booklet with information about persistent postsurgical pain, an overview of the 4-week program, and a description of the strategies. Participants in the EG will receive reminders as needed, that is, if they do not view the weekly session at all.

The intervention will start upon follow-up with the cardiac surgeon (usually approximately 2-4 weeks after surgery). This time frame will allow participants to recover from surgery, return to their routine at home, and experience the challenges of managing persistent pain in their home and daily activities. The intervention will end approximately 6-8 weeks after surgery but before pain is considered chronic (ie, 3 months postsurgery). At the time of enrollment, participants will receive education via telephone and email on how to access and implement the brief web-based MBCT intervention or the attention control intervention. Participants will be informed that weblinks (Qualtrics) for each weekly session will be sent via SMS text messaging or email. The link will redirect participants to a Qualtrics page where video and audio recordings are posted. Qualtrics allows viewing videos from any type of device, for example, a computer, tablet, or smartphone. Participants’ progress and adherence will be monitored on web using Qualtrics.

### Data Collection

As mentioned, measures will be taken via a telephone interview using Qualtrics for data entry. Given the pilot nature of this study and the timeline of the CPSP trajectory [85], all measures, except for acceptability and feasibility of the intervention, will be taken before the intervention (T0), after the intervention (T1), 3 months after surgery (T2), and 6 months after surgery (T3) for both groups [85]. Usual sociodemographic variables (ie, age, sex, civil status, living conditions, education level, and employment status) will be assessed. Relevant medico-surgical information during hospitalization will be collected: type of surgery, presence of postoperative complications, length of hospital stay, and current involvement in a rehabilitation program. The presence of chronic pain before surgery will also be documented. Considering established relations between pain, anxiety, and depression [86-88], measures of anxiety and depression will be taken with the Patient Health Questionnaire-4 for depression and anxiety [89] at all time points. The validity and reliability of the Patient Health Questionnaire-4 has been well established [89-91].

### Intervention Acceptability and Feasibility

An assessment of the acceptability of the intervention will be conducted at the end of the intervention (T1) using a questionnaire. Furthermore, 30-minute semistructured individual interviews (telephone or videoconference) will then be conducted by the RA. The intervention components will be rated in terms of four attributes: (1) appropriateness in helping patients manage pain, (2) effectiveness in promoting pain self-management, (3) suitability, and (4) willingness to adhere with the use of the treatment acceptability and preference measure [92,93]. The ratings refer to a 5-point scale ranging from 0 (not at all) to 4 (very much). A total scale score between 0 and 4 was obtained as the mean of the four items to reflect perceived intervention acceptability. The four items demonstrated internal consistency reliability (α>.80) [93] and were validated in this population when used to assess the first module of the intervention [39]. The patients’ rating of each component will be used to solicit feedback on the acceptability of the intervention and on the need for further modifications during interviews. The interviews will be digitally recorded and transcribed by a trained RA. Regarding feasibility, in addition to refusal, dropout, and withdrawal rates, field notes will be taken during testing regarding various criteria: fidelity in terms of planned mode, dose, timing, and activities, but material resources and context [92]. Percentages of participants completing the sessions according to the planned schedule and the number of times the sessions were accessed by participants will be assessed through Qualtrics monitoring.

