### Study Design

A double-blinded pilot RCT will be used to assess the brief web-based MBCT intervention in the 6 months following cardiac surgery (coronary artery bypass grafting and valve replacement). This study received ethical approval from the institutional review board of Florida State University in January 2021. An experienced research assistant (RA) will be responsible for participants’ recruitment and informed consent procedures at the time of follow-up with the surgeon (usually 2-4 weeks after surgery). The study will be advertised in the surgeon’s offices and surgical units with posters and flyers. Social media platforms and newspapers will also be used. If interested, potential participants will contact the RA via telephone or email, and the inclusion criteria will be assessed. After baseline measures have been collected, participants will be randomized into two groups by the principal investigator (PI): one receiving both the brief 4-week web-based MBCT intervention and the usual care procedure (experimental group [EG]); the second group receiving only one standardized educational web-based session in the first week along with weekly reminders for 3 weeks and the usual care procedure (attention control group [ACG]). At the end of the intervention, participants will be asked if they received the intervention to evaluate their blinding. Participants from the ACG will be given the opportunity to receive the entire intervention once the study is complete.

Computer software will generate the randomization schedule: permuted block randomization with block sizes of 4 and an allocation ratio of 1:1. The randomization list and opaque sealed envelopes numbered sequentially will be prepared by the PI’s colleague who will not be involved in this study. The RA who will be responsible for the entire data collection will be blinded to the patient group assignment. Participants in both groups will receive gift cards of US $25 at each of the four data collection time points (baseline, after intervention, 3 months after surgery, and 6 months after surgery) for a total of US $100.

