### Statistical Analysis

With regard to the first aim, the intervention acceptability scores will be summarized using descriptive statistics. Qualitative data obtained from individual interviews will be analyzed [108] using NVivo software. A preliminary generation of codes or categories based on acceptability attributes from the treatment acceptability and preference measure (ie, appropriateness, effectiveness, suitability, and willingness to adhere) will be used. Double coding will be conducted by the PI and RA. The results will be compared and discussed until a consensus is reached. Frequency counts will also be used to confirm the emergence of themes. Triangulation of both qualitative and quantitative data will be used to develop a more comprehensive understanding of the acceptability of the intervention.

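### The research assistant declared blinded also conducts the T1 interviews about the intervention, so outcome assessment is not blinded at 3 and 6 months

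*Protocol article*

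**What the plan says.** Under Study Design, the article gives the label: "A double-blinded pilot RCT will be used to assess the brief web-based MBCT intervention in the 6 months following cardiac surgery". It introduces one assistant ("An experienced research assistant (RA) will be responsible for" recruitment and consent) and then states: "The RA who will be responsible for the entire data collection will be blinded to the patient group assignment". The PI randomises after baseline, and participants are asked at the end of the intervention whether they received it.

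Under Intervention Acceptability and Feasibility: "An assessment of the acceptability of the intervention will be conducted at the end of the intervention (T1) using a questionnaire". The next sentence reads: "Furthermore, 30-minute semistructured individual interviews (telephone or videoconference) will then be conducted by the RA". The content of the interview is also fixed there, in that the participant's "rating of each component will be used to solicit feedback on the acceptability of the intervention". On handling of the recordings: "The interviews will be digitally recorded and transcribed by a trained RA".

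Under Statistical Analysis, for the same interviews: "Double coding will be conducted by the PI and RA". That section also puts the main interest for effects on chronic postsurgical pain (intensity, interference, opioid use) at 3 and 6 months. Data Collection has all outcome measures taken by telephone interview at T0, T1, T2 (3 months) and T3 (6 months).

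**The concern.** The article promises a blinded outcome assessor and gives that same role a task that discloses the allocation partway through follow-up. The effect outcomes are self-reports spoken to an interviewer. An interviewer who has already heard what the participant thought of the therapy can influence later answers through tone, prompting or expectation, and the participant may want to please someone with whom the programme was discussed. Assessor blinding is meant to protect against the first of these, and by 3 and 6 months it is no longer in place. A reader who takes the double-blinded label at face value would trust the 3- and 6-month estimates more than the design allows. The article intends its estimates of mean and variance to help plan a larger trial, and it will present treatment effects with confidence intervals.

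**Working it through.** The plan gives no figure to reproduce here. The check compares roles, content and timing across sections.

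**1. Is it the same person?** Study Design introduces one RA and gives the RA the entire data collection. The acceptability section names the interviewer as the RA, with the definite article. Only transcription goes to an RA with the indefinite article, who may be someone else. No separate interviewer is named.

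**2. Does the interview reveal the arm?** Per Treatment Conditions, the experimental group has four sessions of 15 to 30 minutes with body scan, mindful breathing and a short breathing exercise. The control group has one 15-minute educational session and three reminders. The article does not say which participants are interviewed:
- If both arms are interviewed, a discussion of each component shows which programme was received.
- If only the experimental arm is interviewed, being interviewed identifies the arm.
- If only some participants in each arm are interviewed, those participants are unblinded to the RA.

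**3. When does this happen?** The intervention starts 2-4 weeks after surgery and lasts 4 weeks: 2 + 4 = 6 and 4 + 4 = 8 weeks, which agrees with the stated end at about 6-8 weeks. The interview is placed after the T1 questionnaire, with no later date given. Taking 3 months as 13 weeks and 6 months as 26 weeks:
- T2 comes 13 − 8 = 5 to 13 − 6 = 7 weeks after the end of the intervention.
- T3 comes 26 − 8 = 18 to 26 − 6 = 20 weeks after it.

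**4. Which assessments are affected?**

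| Assessment | Relation to the interview | Assessor blinding |
|---|---|---|
| T0 | before randomisation | intact |
| T1 | same time point, order not stated | not settled |
| T2 (3 months) | after | lost for those whose arm is revealed |
| T3 (6 months) | after | lost for those whose arm is revealed |

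Two of the three post-randomisation assessments follow the interview, and they are the two of main interest.

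**5. Is there a safeguard elsewhere?** The blinding check concerns participants, not the RA. If the RA asks that question, it is a further cue. No section describes a separate T2/T3 assessor or a delay of the interviews.

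**6. How large is the effect?** The document contains nothing from which a bias in pain scores could be calculated.

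**The case against.** **This is a pilot.** Its first aim is acceptability and feasibility, which this problem does not bias. The effect analyses are described as illustrative, in a study acknowledged not to be powered for significance. This stands and lowers the severity. It does not make the blinding statement correct.

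**The outcomes are participant ratings.** Pain, interference, catastrophizing and acceptance are scored by the participant on fixed scales, so the RA does not judge the score. This also stands. What remains is indirect interviewer influence.

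**Another RA may be involved.** This is a condensed article, and the wording on transcription allows a second assistant. But that wording covers transcription only. If a second person was meant to interview, one added sentence would settle it.

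**The limits of blinding are acknowledged.** Choice of Comparators concedes that double blinding is hard in psychosocial trials and that an attention control helps only partly. That remark concerns the comparator and does not qualify the claim about the RA.

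Two stronger readings are tempting and are not supported:

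- *Coding as an unblinding event before T2.* The article gives no date for coding, and it could follow T3. Only the interview carries the point.
- *Prediction of upcoming allocations.* The RA also recruits and blocks have a fixed size of 4, so a reader might infer that the RA could foresee assignments. By this route, however, the RA learns an allocation only about 4 weeks after it is made. Assume recruitment from the start of June 2021 and completion at the end of March 2022. Then the last surgery falls about the end of September and the last enrolment in late October, some 21 weeks after the start. That gives 32 / 21 ≈ 1.5 enrolments per week, or about 6 in 4 weeks, so a block would usually be full before its first member is interviewed. Certain prediction would need recruitment to stall for about 4 weeks inside a block after at least two of its members were randomised. The article reports slow recruitment but gives no actual rate. Allocation also uses opaque sealed envelopes, prepared by a colleague outside the study.

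**Conclusion.** The point holds as a contradiction in the current text. The RA said to be blinded for all data collection is assigned a T1 interview that reveals the arm, before collecting the T2 and T3 outcomes. Assessor blinding is therefore not a property of this design at 3 and 6 months. This should be fixed, but it does not threaten the pilot's feasibility aim, and no confirmatory claim depends on it.

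The conclusion rests on three assumptions: the RA denotes one person throughout, the interviews take place shortly after T1 as the text implies, and discussing components discloses the arm. The third is close to certain; the first two are the natural reading. A reader might infer that the T2 and T3 results will be biased by some material amount. The documents show only that the protection is absent, and the direction and size of any bias are unknown.

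**What to change.** - Have the PI, who already randomises, conduct the T1 interviews in place of the RA who collects outcomes.
- At T1, complete all outcome scales before any question on acceptability or on which intervention was received.
- Keep the RA out of coding until that RA's T3 collection is finished.
- If this is not done, state that outcome assessment is unblinded after T1 and drop the double-blinded label.

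The cost is a reassignment of existing staff and a fixed order of questions at one contact. The small downside is that participants may speak less candidly to the PI, which bears on the acceptability aim. Moving only T2 and T3 to self-completion is not a good substitute: it would change the mode of collection partway through a longitudinal model whose baseline was taken by telephone.

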### Pain

Pain intensity is a global indicator of pain. It will be assessed using a numerical rating scale (0-10), with the anchors being *no pain at all* (score=0) and *worst possible pain* (score=10). This type of scale is recognized for its reliability, validity, and sensitivity in various clienteles and settings, including patients undergoing cardiac surgery [79,94,95]. Four different measures of pain intensity will be taken: (1) average pain upon movement in the past 7 days, (2) worst pain upon movement in the past 7 days, (3) present pain upon movement, and (4) present pain at rest.

### Pain Interference With Daily Activities

As suggested by the Initiative on Methods, Measurement, and Pain Assessment in Clinical Trials group with regard to pain core domains in clinical trials [79,96], the impact of pain on various aspects of daily living will be assessed with interference items of the Brief Pain Inventory [97]. The Brief Pain Inventory has been successfully validated in patients undergoing cardiac surgery in the context of both acute and chronic pain and intervention research [66,98,99]. It includes 7 items and evaluates the impact of pain on general activity, mood, walking, work, relationships, sleep, and enjoyment of life. Some items were added in earlier studies to measure postoperative pain-related interference with appetite, concentration, and breathing or coughing [66,99]. Each item represents a subscale and can be scored (range: 0-10) and analyzed individually, with the anchors being *does not interfere* (score=0) and *completely interferes* (score=10). The total interference score can also be calculated by considering the sum of all items.

### Opioid Use and Misuse

Analgesic medication intake will be documented at all time points. If some participants report that they currently take opioids, they will complete the Opioid Compliance Checklist [100] on opioid misuse. This instrument is a brief self-report measure comprising eight items with a yes or no answer. A greater number of positive answers reflects an increased risk of current and future opioid misuse. Its validity and reliability in detecting drug-related behaviors have been well established [101].

### Mindfulness, Chronic Pain Acceptance, and Pain-Related Catastrophic Thoughts

Given that the intervention is meant to increase mindfulness and the associations between mindfulness measures, pain acceptance, and pain-related catastrophic thoughts [21,61,62], mindfulness will be assessed. The Cognitive and Affective Mindfulness Scale-Revised [102] will be used to assess mindfulness. This 12-item scale captures the broad concept of mindfulness according to four domains (attention, present focus, awareness, and acceptance or nonjudgement) without being specific to any type of meditation or strategy. Each item is rated on a 4-point scale with the end points *rarely or not at all* (score=1) and *almost always* (score=4). The total score is calculated by taking the sum of the items. The Cognitive and Affective Mindfulness Scale-Revised has demonstrated good consistency for the overall score [102] and has been validated with MBI in patients with persistent pain [50]. The Chronic Pain Acceptance Questionnaire-8 [103] is an 8-item questionnaire measuring chronic pain acceptance. This scale comprises two subscales: the degree to which patients engage in daily living activities regardless of pain (4 items) and willingness to experience pain (4 items). It has demonstrated good consistency, and its sensitivity to therapeutic changes has been validated [104]. The Pain Catastrophizing Scale [105] will be used to assess patients’ pain-related catastrophic thoughts. It includes 13 items divided into three subscales: rumination (4 items), magnification (3 items), and helplessness (6 items). Each item is rated on a 5-point scale with the end points *not at all* (score=0) and *all the time* (score=4). The total score and scores for each subscale can be calculated by taking the sum of the items. The Pain Catastrophizing Scale has demonstrated an excellent internal consistency [105], and its sensitivity to psychosocial interventions for chronic pain has been established [106,107].

### Statistical Analysis

With regard to the first aim, the intervention acceptability scores will be summarized using descriptive statistics. Qualitative data obtained from individual interviews will be analyzed [108] using NVivo software. A preliminary generation of codes or categories based on acceptability attributes from the treatment acceptability and preference measure (ie, appropriateness, effectiveness, suitability, and willingness to adhere) will be used. Double coding will be conducted by the PI and RA. The results will be compared and discussed until a consensus is reached. Frequency counts will also be used to confirm the emergence of themes. Triangulation of both qualitative and quantitative data will be used to develop a more comprehensive understanding of the acceptability of the intervention.

Regarding the preliminary effects of the intervention, the protocol will favor an intention-to-treat approach for the analysis of results, thus involving all patients who were randomly assigned. Participants’ flow will be reported according to the Consolidated Standards of Reporting Trials guidelines for psychological interventions [109]. The statistical analysis will be mostly descriptive (mean and SD for continuous outcomes and frequency and proportion for categorical outcomes) with 95% CIs when appropriate. Pain intensity, pain interference, opioid use, mindfulness, pain acceptance, pain-related catastrophic thoughts, and depression or anxiety scores will be summarized using descriptive statistics presented per group at each time point. Furthermore, treatment effects will be estimated and presented with 95% CIs at each time point. Between-group differences will be assessed by fitting linear mixed models for each outcome: pain intensity, pain interference, opioid use, mindfulness, pain acceptance, pain-related catastrophic thoughts, and anxiety or depression. Outcome variables will be regressed on the intervention group (EG vs ACG) and time (preintervention, postintervention, and 3 and 6 months after surgery) after covarying baseline values to perform statistical matching on prerandomized values, thus ensuring that comparisons by treatment group are independent of baseline differences [110]. Of primary interest is the impact of the intervention on the prevalence and severity of CPSP (ie, pain intensity, pain interference, and opioid use) at 3 and 6 months. However, these analyses will be undertaken primarily for illustrative purposes, as the study is not powered to show statistical significance. An α level of significance of .05 will be used for all analyses.

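### The mixed model uses the preintervention value both as an outcome row and as a covariate, and names no group-by-time term; fitted with the named terms only it understates the effect, and with an interaction added its standard errors are still too small.

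*Protocol article*

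**What the plan says.** All of this is in the Statistical Analysis section of the protocol article, unless another section is named.

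- Model class: "Between-group differences will be assessed by fitting linear mixed models for each outcome". No covariance structure is given.
- Predictors: outcomes are to be "regressed on the intervention group (EG vs ACG) and time (preintervention, postintervention, and 3 and 6 months after surgery) after covarying baseline values", so time has four levels and the first of them is T0.
- Baseline: the model is fitted "after covarying baseline values to perform statistical matching on prerandomized values", with the stated aim of "ensuring that comparisons by treatment group are independent of baseline differences".
- Promised output: "treatment effects will be estimated and presented with 95% CIs at each time point".
- Priority: "Of primary interest is the impact of the intervention on the prevalence and severity of CPSP", at 3 and 6 months.
- Status: the section describes these comparisons as mainly illustrative, because the trial lacks the power for significance testing.

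The Data Collection section defines four measurement times: T0 before the intervention, T1 after it, and T2 and T3 at 3 and 6 months after surgery. The Study Design section has T0 measured before randomization.

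**The concern.** Two features of the model sentence conflict with its purpose.

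First, a baseline measurement can be an outcome row or a covariate, but not both in the same model. At T0 the outcome equals its own covariate. Randomization comes afterwards, so the expected group difference in that row is zero. The row says nothing about treatment, yet it counts as a fourth visit. It can pull a pooled group coefficient towards zero, and it lowers the estimated residual variance because it is almost fully explained.

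Second, a model with group and time as main effects returns one group coefficient. It cannot supply a separate effect at each visit, nor the 3- and 6-month effects that matter most.

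At stake are the estimates and intervals for the second aim in the Objectives section (preliminary effects), since this one specification serves every outcome under that aim. The first aim, acceptability and feasibility, is untouched.

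**Working it through.** The protocol states no figure for the model coefficient, so there is none to reproduce. The sentence can be read in two ways, and the check takes each in turn.

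**Inputs from the protocol article:** four visits, one before and three after the start of intervention; T0 measured before randomization; 16 per group; 30% attrition anticipated by 6 months (Settings and Participants).

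**Assumptions (not in the protocol):** random intercept; outcome SD 2; equal correlation rho between visits, 0.5 unless stated; true effect -1.0 at T1, T2 and T3; dropout of 10%, 20% and 30% at T1, T2 and T3 where used.

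**Reading A: only the named terms (group, time, baseline).**

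1. With complete data and a random intercept, group and baseline vary only between patients. The group coefficient is therefore that from regressing each patient's four-visit mean on group and baseline.
2. The four-visit mean is (Y0 + Y1 + Y2 + Y3)/4. Given Y0, the first term has no group effect, so the coefficient estimates (0 + d1 + d2 + d3)/4, where d1 to d3 are the effects at T1 to T3. That is 3/4 of the mean post-baseline effect.
3. With d1 = d2 = d3 = -1.0 this gives -3/4 = -0.75. The factor does not depend on rho. In data simulated with rho 0.3, 0.5 and 0.7, under both equal and first-order autoregressive correlation, the ratio to the model without the T0 row was 0.750 in all six complete-data cases.
4. At 16 per group, the simulated coefficient averaged -0.75 to -0.76, with 87-90% coverage of the nominal 95% interval. Removing the T0 row gave -1.00 to -1.02 and 95%.
5. Under the assumed dropout, T0 is a larger share of the rows. A simple row count gives (0.9 + 0.8 + 0.7)/(1 + 0.9 + 0.8 + 0.7) = 2.4/3.4 = 0.71. The fitted ratio was 0.685 to 0.702, an attenuation of about 30-31%.

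**Reading B: a group-by-time term is added, T0 stays as an outcome row.**

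1. Each visit now has its own group effect. In large simulated samples the T0 effect was about 0 and those at T1, T2 and T3 about -1.0 each, so there is no bias.
2. The common baseline slope is pulled towards 1 by the T0 row. It becomes (1 + 3 rho)/4 = (1 + 1.5)/4 = 0.625, where the slope for the post-baseline visits is 0.5.
3. Residual variance at T0: (1 - 0.625)² × 4 = 0.5625. At each later visit: 4 × (1 - 0.5²) + (0.5 - 0.625)² × 4 = 3.0625.
4. A random-intercept model uses one total variance for all visits: (0.5625 + 3 × 3.0625)/4 = 2.4375. The reported 6-month standard error is √(2.4375 × 2/16) = 0.55.
5. The actual standard deviation of that estimate is √(3.0625 × 2/16) = 0.62. The model with T1 to T3 only gives √(3 × 2/16) = 0.61. The reported value is 0.552/0.612 = 0.90 of the second and 0.552/0.619 = 0.89 of the first, so it is 10-11% too small.
6. The interval's half-width is 1.96 × 0.89 = 1.75 true standard deviations, which is coverage of about 92%. Simulations gave roughly 91-94%.

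**The case against.** The strongest reply is that the attenuation depends on a term being absent, and the article never says that only main effects are fitted. It promises an effect at each time point, which a single pooled coefficient cannot deliver, so an intended interaction is a fair inference. A condensed article may also leave the full list of model terms to a fuller document. This stands. A reader might infer that the plan as published is bound to understate the effect by 25%, and the text does not support that without conditions. The figure needs the interaction to be left out, a random intercept and complete data, none of which the article fixes.

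A reader might also take an effect that builds over time as a measure of the damage. With effects of 0, -0.5 and -1.0, reading A gives (0 + 0 - 0.5 - 1.0)/4 = -0.375 against a 6-month effect of -1.0. Most of that gap is not due to the T0 row. A main-effects model on T1 to T3 alone would give (0 - 0.5 - 1.0)/3 = -0.50, so 0.50 of the 0.625 shortfall comes from averaging over visits and 0.125 from T0.

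Finally, a reader might infer that this coefficient is what the next trial will be planned on. Settings and Participants ties that planning to means and variances, and the per-group descriptive summaries at each visit do not depend on this model. No confirmatory claim rests on it either.

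The reply does not dispose of the double use of baseline. That is written into the model sentence, not left out of it, and adding the interaction does not repair it.

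**Conclusion.** The specification is wrong as written, with a limited consequence. T0 is both an outcome row and its own covariate, and the named terms do not yield the visit-specific effects that the section promises.

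Which error results depends on what is fitted. Without an interaction, the result is a biased pooled estimate. With one, the estimates are sound but the 6-month interval is too narrow. The size of the second error rests on the assumed equal correlation and random intercept. An unstructured covariance would not be a way out, because the T0 row is fully explained by its own covariate and the fit would be degenerate.

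The analyses are declared illustrative, and the descriptive results and the feasibility aim are unaffected. This is a should-fix for the preliminary-effects aim, to be settled before the data are analyzed.

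**What to change.** Amend the model sentence in one of two ways.

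- Use T1, T2 and T3 as the only outcome rows. Fit baseline value, group, time and group-by-time, and report the group contrasts at T2 and T3 with 95% CIs (T1 alongside, to meet the promise of an effect at each visit). A baseline-by-time term is optional.
- Or keep all four time points in a constrained longitudinal model with a baseline mean common to both groups and no baseline covariate, and report the same contrasts.

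Either version keeps the adjustment for chance baseline differences that the section wants. The cost is one sentence in the protocol or analysis plan, with no new data, no more participants and no change in design.
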